## Abstract

**Aim:**

This article is a report of a study protocol designed to examine the effects of guided clinical reasoning on the quality of the Advanced Nursing Process—the evidence‐based version of the traditional nursing process. It aims to describe the theoretical framework—Kirkpatrick's evaluation model, the key concepts and the instruments for the planned study.

**Design:**

A complex experimental intervention study using data and method triangulation is proposed.

**Methods:**

Registered Nurses (*N* = 92), nursing records (*N* = 180) and 24 patients will be included. Nurses’ knowledge and attitude will be evaluated by questionnaires/tests, their clinical performance by observations. Patients’ perspective will be addressed by qualitative interviews and patient records by using the instrument Quality of Diagnoses, Interventions and Outcomes revised (Q‐DIO R).

**Discussion:**

Kirkpatrick's model (including quantitative and qualitative methods) is providing evaluations from different perspectives on the quality of the Advanced Nursing Process and on intervention effects.

## INTRODUCTION

1

Nursing care must be transparently described due to financial, legal (Health Insurance Act—KVG, 2016) and professional requirements (Müller‐Staub, Abt, Brenner, & Hofer, 2015). This can be achieved by applying and documenting the nursing process with standardized nursing languages (SNLs) (Escalada‐Hernández et al., 2015; Estrada & Dunn, 2012; Hariyati, Yani, Eryando, Hasibuan, & Milanti, 2016; Jones, Lunney, Keenan, & Moorhead, 2010; Pérez Rivas et al., 2016). This approach increases patient safety and leads to better nursing‐sensitive outcomes (Pérez Rivas et al., 2016). However, nurses face challenges in clearly documenting the nursing process. Several studies on nursing process documentation have shown clinically relevant deficits, with the consequences of impaired patient well‐being, lower care quality, including risks to patient safety (De Marinis et al., 2010; Gershater, Pilhammar, & Alm Roijer, 2010; Pereira et al., 2015; Zegers et al., 2011). The application of the nursing process based on SNLs is a challenging task and should be fostered through educational interventions. guided clinical reasoning (GCR) could be a useful method for this purpose (Müller‐Staub, Needham, Odenbreit, Lavin, & Achterberg, 2008). The aim of this protocol is to describe a comprehensive methodological paper demonstrating a research plan including its theoretical framework—Kirkpatrick's evaluation model—the key concepts Advanced Nursing Process and the study intervention GCR along with the instruments for data collection.

## BACKGROUND

2

The nursing process provides a systematic approach for nursing care (American Nurses Association [ANA], 2015a). This relationship and problem‐solving process were further developed into an extended, deepened and research‐based version, so‐called Advanced Nursing Process. It “consists of defined, validated concepts. It includes assessment, nursing diagnoses, nursing interventions and nursing outcomes that are rooted in scientifically based nursing classifications” (Müller‐Staub et al., 2015, p. 13). Compared with the “traditional nursing process” without SNLs, the Advanced Nursing Process contains valid assessment tools and evidence‐based diagnoses, intervention and outcome concepts (=SNLs) as described in nursing classifications. The classification systems that best meet literature‐based validity and reliability criteria are the NANDA‐International Diagnoses Classification (NANDA‐I), the Nursing Outcomes Classification (NOC) and the Nursing Interventions Classification (NIC) (Odenbreit, Müller‐Staub, Brokel, Avant, & Keenan, 2013) (for abbreviations, see Table 1). These three classifications are linked and are referred to as the NANDA‐I, NIC and NOC (NNN) taxonomies (Johnson et al., 2011). The NNN taxonomies are recognized by the ANA (2015b) for their use in Electronic Health Records (as interface terminologies), as multidisciplinary reference terminologies in the Systematized Nomenclature of Medicine—Clinical Terms (SNOMED CT) and as well as Logical Observation Identifier Names and Codes (LOINC) for communicating similar meaning across different software systems and different settings. The application of the NNN taxonomy relies on clinical decision‐making including diagnostic, therapeutic and ethical judgements (Gordon, ; Müller‐Staub et al., 2015). After implementation of the Advanced Nursing Process, nurses stated more accurate nursing diagnoses and performed more effective interventions that led to better patient outcomes (Müller‐Staub, Needham, et al., 2008; Pérez Rivas et al., 2016). However, previous studies demonstrated deficits in the application of the Advanced Nursing Process, including severe documentation errors. Missing assessments, inaccurate nursing diagnoses and inconsistencies between diagnoses, interventions and outcomes have been reported (Gershater et al., 2010; Halvorsen, Eide, Sortland, & Almendingen, 2016; Kebede, Endris, & Zegeye, 2017; Paans, Sermeus, Nieweg, Krijnen, & Schans, 2012). For instance, only 36% of nursing diagnoses recognized by Registered Nurses (RNs) were documented in the nursing records (Kobleder, 2011). A considerable consequence of such deficiencies is impaired clinical decision‐making, which leads to less positive nursing‐sensitive outcomes (Paans, Sermeus, Nieweg, & Schans, 2010; Saranto & Kinnunen, 2009; Zegers et al., 2011). Gershater et al. (2010) also reported negative medical, professional and economic consequences. Many factors can lead to rudimentary applications of the Advanced Nursing Process*.* These factors were specifically identified in individuals (deficient nurse knowledge and attitude), in the social context (organizational culture and institutional structures) and in financial limitations (Grol & Wensing, 2013). Nurses need patient‐related knowledge in addition to knowledge regarding diagnostic concepts, evidence‐based interventions and outcomes (Lunney, 2010; Paans, Nieweg, van der Schans, & Sermeus, 2011). Nurses’ attitude towards the nursing process is seen as a major influencing factor on its application (Ajzen, 2012; Romero‐Sánchez, Paloma‐Castro, et al., 2013; Romero‐Sánchez, Paramio‐Cuevas, et al., 2013) and on diagnostic prevalence and accuracy (Collins, 2013; Paans et al., 2011). In addition, electronic and handwritten nursing records have been identified as obstacles: nursing diagnoses have been inaccurately documented, and nurses have been found to be unfamiliar with SNLs (Conrad, Hanson, Hasenau, & Stocker‐Schneider, 2012; Paans et al., 2012). With respect to organizational factors, the attitude of supervisors towards nursing diagnoses has been reported in previous studies as a significant influencing factor (Axelsson, Björvell, Mattiasson, & Randers, 2006; Westendorf, 2007) and also, organizational factors, such as staff turnover (particularly of nurse leaders), nurse–patient ratio, workload level and nursing organization systems, influence nurses’ diagnostic competencies and their performance of the nursing process (Paans et al., 2011).

**Table 1 nop2299-tbl-0001:** Meaning of abbreviations

APN	Advanced Practice Nurse
GCR	Guided clinical reasoning
NANDA‐I	NANDA‐International Diagnoses Classification
NIC	Nursing Interventions Classification
NNN	Linked classifications of NANDA‐I, NIC and NOC
NOC	Nursing Outcomes Classification
PND	Positions on Nursing Diagnoses Scale
Q‐DIO (R)	Instrument Quality of Nursing Diagnoses, Interventions and Outcomes (revised)
SNL	Standardized nursing language

Several educational interventions were performed to develop nurses’ knowledge, their attitude and skills to improve the application of the Advanced Nursing Process. Nursing process‐based simulation trainings (Kim & Shin, 2016), with or without simulated patients or nursing records, were implemented (Bolstad, Xu, Shen, Covelli, & Torpey, 2012; Karadag, Caliskan, & Iseri, 2016; Lambie, Schwend, & Scholl, 2015) as well as multi‐day trainings with case studies/case discussions (Bruylands, Paans, Hediger, & Müller‐Staub, 2013; Müller‐Staub, Needham, et al., 2008), from 12 hr (Collins, 2013), over 5 days (Odutayo, Olaogun, Oluwatosin, & Ogunfowokan, 2013) to 10 days (Patiraki, Katsaragakis, Dreliozi, & Prezerakos, 2017). Each educational intervention has shown at least partial improvements in nurses’ knowledge, attitude and/or skills required for clinical reasoning and writing meaningful care plans.

### Theoretical framework of the study

2.1

#### Guided clinical reasoning

2.1.1

Guided clinical reasoning will be used as study intervention. GCR is an educational approach aiming to improve nurses’ diagnostic competencies to state accurate nursing diagnoses and to link these with effective nursing interventions to achieve favourable patient outcomes. It is an interactive teaching method that is based on constructivist theories (Müller‐Staub, 2007; Siebert, 1999) and Balint's case supervision (Müller‐Staub, 1992). These approaches were further developed and combined with the diagnostic process by Müller‐Staub (Bruylands et al., 2013; Müller‐Staub, Needham, et al., 2008). GCR is applied in case meetings and contains five working stages (Figure 1). GCR must be led by a moderator with strict, straightforward rules. In the preliminary phase (a), several patients (termed cases) are briefly introduced to prepare all participants for the case meeting. In the second phase (b), a negotiation process leads to case selection. Then (c), the case provider further presents his/her case by freely telling those present about his/her experiences with the patient in an unstructured manner. In the case‐processing phase (d), the participants are individually asked by the moderator to communicate their spontaneous thoughts and associations. The moderator asks questions to aid his/her analysis, leading to hypotheses concerning the patients’ nursing diagnoses. In each round, the case presenter gives deeper insights on the patient by building on the participants’ reflections/assumptions. No discussion or problem‐solving suggestions are allowed at this stage. This “working phase” continues until a clear picture of the case arises. Finally, a meta‐perspective (e) and hypothetical nursing diagnoses are stated. In the case evaluation phase, the participants compare the hypothetical nursing diagnoses using SNL. The moderator asks questions such as, “Does the definition of the nursing diagnosis describe the case? Which of the related factors are seen in the presented case?”. After validating the hypothetical nursing diagnosis in comparison with the SNL, the participants are asked to choose appropriate, SNL‐based nursing outcomes and effective nursing interventions (Bulechek, Butcher, Dochterman, & Wagner, 2016; Doenges, Moorhouse, & Murr, 2014; Moorhead, Johnson, Maas, & Swanson, 2013). The results of the case meeting are put into practice by writing an SNL‐based care plan and evaluating it with the patient. By doing so, the Advanced Nursing Process is performed.

**Figure 1 nop2299-fig-0001:**

The five stages of case‐meeting GCR (Müller‐Staub & Stuker‐Studer, 2006)

Only two studies (record audits) report GCR effects: (a) nursing assessments were improved, (b) nursing diagnoses were more specific and accurate, and (c) nursing interventions were more diagnosis/aetiology‐specific and therefore more effective (Bruylands et al., 2013; Müller‐Staub, Needham, et al., 2008). However, studies examining nurses’ knowledge, attitude and clinical performance before and after GCR are lacking. No clinical observational studies on the effects of GCR on performing the Advanced Nursing Process in practice are available, and patients’ perspectives have not yet been included.

#### Evaluation model

2.1.2

The New world Kirkpatrick model (Figure 2) provides the framework to evaluate the effects of GCR. This model has been widely applied and published to evaluate education programmes; it contains four levels to develop a chain of evidence: Reaction (level 1), Learning (level 2), Behaviour (level 3) and Results (level 4) (Kirkpatrick & Kirkpatrick, 2008, 2010).

**Figure 2 nop2299-fig-0002:**
[figure not shown]
The New world Kirkpatrick model (Kirkpatrick Partners, 2010–2012)

At level 1, a conventional satisfaction survey is conducted with the participants (e.g. nurses). The assumption is that participants can profit only if they are satisfied with the training. An additional satisfaction survey filled out by the supervisor of trainees (e.g. nursing director) is suggested to enhance the validity of results (Kirkpatrick & Kirkpatrick, 2010). At level 2, the knowledge, skills and attitude gained by the participants are examined. Level 1 and level 2 are measured in the learning field (e.g. training sessions). The level 3 evaluation addresses the effects of the GCR intervention on nurses’ behavioural changes in their field of work (their clinical performance on the hospital wards). The study participants, their supervisors and/or others that are familiar with nurses’ performance (e.g. patients, Advanced practice nurses [APNs]) are assessing the transfer results of the study intervention (Kirkpatrick, 1979). The effectiveness of GCR for the institution is measured at level 4: the desired outcomes (the quality of the Advanced Nursing Process). For levels 2–4, the model recommends quantitative pre–post‐test designs and the evaluation across all four levels is indispensable to build a chain of evidence. This means that the findings of data and method triangulation must be synthesized and compared. The evaluation of a programme's effectiveness based on Behaviour (level 3) or on Results (level 4) is useless without the inclusion of Learning (level 2) (Kirkpatrick & Kirkpatrick, 2008).

How are these levels addressed in this planned study? Satisfaction with the GCR intervention (Reaction—level 1) will be measured by a participant satisfaction survey, and the leadership perspective will be covered by an interview with the nursing director. A knowledge test and a self‐assessment instrument will be used to examine nurses’ knowledge and attitude towards the Advanced Nursing Process (Learning—level 2). APNs will observe nurses’ performance of the Advanced Nursing Process in practice to evaluate nurses’ clinical behaviour after GCR (Behaviour—level 3); additionally, patients will be interviewed on their experiences with the nurses’ knowledge, skills and attitudes. The results of the GCR intervention (level 4) will be evaluated by record audits with the Q‐DIO R instrument, which measures the accuracy of nursing diagnoses, the effectiveness of nursing interventions and the quality of patient outcomes. Furthermore, organizational factors will be collected to control possible confounders.

### Objective

2.2

The aim of the planned study was to evaluate the effect of GCR on the quality of the *Advanced Nursing Process* by using Kirkpatrick's 4‐level evaluation model (Kirkpatrick & Kirkpatrick, 2008, 2010).

### Research questions

2.3

The main research question is What effect does GCR have on the Advanced Nursing Process? According to the operationalized levels of the Kirkpatrick model, the detailed research questions are
How do the participating nurses and the nursing director rate GCR? (Reaction)What effect does GCR have on nurses’ knowledge and on their attitude towards the Advanced Nursing Process in the learning field? (Learning)What effect does GCR have on nurses’ clinical performance and attitude towards the Advanced Nursing Process on the wards? How do patients describe their experience of the Advanced Nursing Process (nurses’ knowledge, skills and attitudes)? (Behaviour)What effect does CGR have on the accuracy of nursing diagnoses (including frequency and variety), the effectiveness of nursing interventions and the quality of nursing outcomes? (Results)Are the findings of data and method triangulation (satisfaction, knowledge, attitude, Q–DIO R scores, APNs and patients’ perspective on nurses’ clinical performance) mutually supportive to build a chain of evidence?

### Hypotheses

2.4

After GCR, nurses in the experimental group will have a significantly higher total score in the knowledge test and a significant more positive attitude towards the Advanced Nursing Process on the Positions on the Nursing Diagnoses (PND) Scale than those in the control group.After GCR, in the experimental group the congruence between observations of direct care, patients’ statements and nursing records will be greater than that in the control group.After GCR, in the experimental group the quality of nursing diagnoses, interventions and outcomes in record audits (measured by Q‐DIO R) will be significantly higher than that in the control group.

## METHODS

3

### Study design and setting

3.1

A complex experimental intervention study using data and method triangulation will be performed. A complex intervention contains a “number of interacting components […], number and difficulty of behaviours required by those delivering or receiving the intervention, number of groups or organizational levels targeted by the intervention, number and variability of outcomes [and] degree of flexibility or tailoring of the intervention permitted” (Craig et al., 2008). General teaching and learning processes as well as GCR are guided and influenced by teachers’ and participants’ behaviour and various context conditions. Furthermore, the knowledge transfer from the learning field to the work field including organizational influencing factors will be considered, and therefore, several outcomes on different levels will be measured. Quantitative methods will be used to take knowledge tests and self‐assessments on nurses’ attitude towards the Advanced Nursing Process. The quality of the Advanced Nursing Process—including the accuracy, frequency and variety of nursing diagnoses—will be evaluated by nursing record audits with the Q‐DIO R instrument. However, a general criticism is how the nursing reality is represented in the nursing records. Therefore, to the objectives of level 3 evaluation, observations of nurses’ clinical performance of the Advanced Nursing Process, interviews with patients and qualitative document analyses will be performed to verify the Q‐DIO results (Kirkpatrick & Kirkpatrick, 2008, 2010).

The study will be conducted in a Swiss public hospital. From a total of 12 wards, seven fulfil the inclusion criteria in that they are acute geriatric (2), internal medicine (3) or surgical (2) inpatient wards. By sealed‐envelope drawings, three wards will be randomly allocated to the experimental group, three to the control group and one will be excluded.

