#### Nursing records

3.2.2

By using a web‐based random generator, a sample of nursing records (*N = *180) will be drawn (https://www.random.org/). Nursing records covering at least 4 days and at least one nursing diagnosis will be selected from all six wards (experimental group *N = *90, control group *N = *90). The sample‐size calculation was performed using *t*‐tests for unpaired samples (one‐sided) and bases on previous results for using the Q‐DIO for all three sub‐concepts of the instrument (nursing diagnoses, interventions and outcomes) (Müller‐Staub, Needham, et al., 2008). An effect size of 0.5 (mean) on a scale from 0–4 is assumed. For nursing diagnoses, 32 nursing records per group are required; we assumed an effect size of 0.63 (power 80%). For nursing interventions, 45 records (effect size, 0.53; power, 80%) are required and for nursing outcomes, 44 records (effect size, 0.47; power, 70%) are required. To ensure an even distribution in the experimental and control groups, 15 nursing records will be selected per ward (*N = *45 records before and 45 records after the study intervention, totalling *N = *90) for each group (Bortz & Schuster, 2016).

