### Data analyses

3.6

The knowledge test and nurses’ attitude (PND scale) will be analysed using descriptive and inductive statistics. Single‐item and total scores will be compared between the two measurement points (Wilcoxon signed‐rank test) and between the experimental and control groups (Mann–Whitney *U* tests). The scores of supplementary control items for the knowledge test will be separately analysed and compared between the two measurement points and the two groups. The results of the three nurses’ attitude measurements (*t*0_2_, *t*1 and *t*2) will be evaluated using Friedman tests (Bortz & Schuster, 2016; Clauß, Finze, & Partzsch, 2011). The free‐text item answers in the knowledge test will be analysed using Mayring's (2010) seven‐step content analyses.

Participant satisfaction will be descriptively analysed based on absolute and relative frequencies and distributions. Content analyses (Mayring, 2010) will be applied to the interview with the nursing director and to the free‐text data from the satisfaction surveys.

The Q‐DIO R scores will be summed for each sub‐concept. If the data are normally distributed, unpaired *t*‐tests are applied to compare pre‐ and postintervention scores and to compare the experimental and control groups. The frequencies and patterns (variety) of the NANDA‐I nursing diagnoses will be compared between the two measurement time points and between the experimental and control groups.

Correlations among nurses’ knowledge, attitude, Q‐DIO R scores, demographic and organizational characteristics will be analysed depending on level of data and testing requirements by Pearson product–moment correlations, Spearman correlations or chi‐squared tests. All tests will be evaluated one‐sided (levels of significance 0.05) using IBM SPSS Statistics 24 (SPSS Inc.).

The qualitative evaluation of nurses’ clinical behaviour will be performed by within‐ and cross‐case analyses (Kuckartz, 2016). Qualitative observations, interviews and nursing records will be analysed using the first and second coding cycles (Saldaña, 2015). Decoding (open) is applied in the first cycle, and encoding (deductive) is applied in the second cycle. For the qualitative data analyses, MAXQDA 12 software (VERBI GmbH, 2015) will be used.

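### As described, the ward draw is not restricted by specialty although the seven wards allow an exact match; 83% of draws leave some imbalance, which the planned tests do not correct

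*Protocol article*

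**What the plan says.** Section 3.1 (Study design and setting) of the protocol article starts from twelve wards, of which "seven fulfil the inclusion criteria in that they are acute geriatric (2), internal medicine (3) or surgical (2) inpatient wards". The allocation takes one sentence: "By sealed‐envelope drawings, three wards will be randomly allocated to the experimental group, three to the control group and one will be excluded". No stratification, pairing or matching by specialty is mentioned. The excluded ward comes out of the same draw, so it may be of any specialty.

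Balance is planned below ward level. Section 3.2.1 asks for a similar mix of grades and skills among the nurses in the two groups. Section 3.2.2 fixes the number of records: "To ensure an even distribution in the experimental and control groups, 15 nursing records will be selected per ward", giving 45 before and 45 after the intervention in each arm.

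Section 3.6 (Data analyses) compares Q-DIO R scores before with after, and experimental with control, by unpaired t-tests if the data are normal. No term for baseline, ward or specialty is stated. Ward characteristics are collected under section 3.5.1.7, but in section 3.6 they enter only through correlations or chi-squared tests.

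**The concern.** Wards are the randomised units, and there are three per arm. With so few, a draw that ignores specialty will usually leave the arms with different specialty mixes, even though the list of eligible wards happens to permit an exact match.

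Specialty is a plausible influence on the outcomes. The article's own background (section 2) names nurse–patient ratio, workload and the organisation of nursing as influences on diagnostic competence and on performance of the nursing process. Section 3.5.1.7 collects length of stay, staffing ratio and skill mix per ward as factors to be controlled. It is reasonable to assume that these differ between geriatric, medical and surgical wards, and that the frequency and variety of nursing diagnoses (among the primary outcomes in section 3.4) follow the type of patient. The article does not itself name specialty as an influence and gives no figure for it.

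At stake is the post-intervention comparison of the arms. Part of any difference, in either direction, could reflect which specialties happened to fall where.

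**Working it through.** **The plan's own figures.** The article states no probability of imbalance. Its related figures are the record numbers in section 3.2.2. For a one-sided unpaired t-test at 0.05, the normal formula is n = 2(z₁₋α + z_power)²/d².

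- Diagnoses (d = 0.63, power 80%): 2(1.645 + 0.842)²/0.63² gives 32; stated 32.
- Interventions (d = 0.53, power 80%): 2(1.645 + 0.842)²/0.53² gives 45; stated 45.
- Outcomes (d = 0.47, power 70%): 2(1.645 + 0.524)²/0.47² gives 43, and the exact noncentral t gives 44; stated 44.

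The figures reproduce from formulas that have no term for ward or specialty.

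**Inputs for the draw (section 3.1).** Two geriatric (G), three medical (M) and two surgical (S) wards; three to each arm and one excluded; all draws assumed equally likely.

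**All draws.** 7!/(3!·3!·1!) = 140.

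**Exact match (1 G, 1 M, 1 S per arm).** The excluded ward must be medical: 3 choices. Each specialty pair can then be split in 2 ways: 3 × 2 × 2 × 2 = 24. So 24/140 = 17.1% are matched and 116/140 = 82.9% are not.

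**Both geriatric wards in one arm.** 2 arms × 5 choices for that arm's third ward × C(4,3) = 4 choices for the other arm: 40/140 = 28.6%. The count for the surgical pair is the same.

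**Either pair in one arm.** Both pairs can be intact only in opposite arms: 2 × 3! ways to place the medical wards = 12. Hence 40 + 40 − 12 = 68, and 68/140 = 48.6%.

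**No specialty in common.** All three medical wards are in one arm (2 ways) and three of the other four wards in the other (C(4,3) = 4): 8/140 = 5.7%.

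**Degree of imbalance**, by wards per arm without a same-specialty counterpart in the other arm (full enumeration):

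| Unmatched wards per arm | Draws | Share |
|---|---|---|
| 0 | 24 | 17.1% |
| 1 | 48 | 34.3% |
| 2 | 60 | 42.9% |
| 3 | 8 | 5.7% |

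**Source of the imbalance.** The excluded ward is medical in 60/140 = 42.9% of draws; otherwise no exact match exists. Always excluding a medical ward but drawing the other six freely would match in 2 × 2 × 2 = 8 of C(6,3) = 20 draws, still leaving 12/20 = 60% imbalanced. Both steps must be restricted.

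**After the restricted draw.** Only the 24 matched allocations remain possible, so specialty imbalance falls from 82.9% to 0%.

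**Price in a ward-level permutation test.** The free draw of six wards has 20 arrangements, so the smallest one-sided p is 1/20 = 0.05. The restricted draw has 2³ = 8, so the smallest is 1/8 = 0.125. The plan's criterion is: "All tests will be evaluated one‐sided (levels of significance 0.05".

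**The case against.** Several objections have force.

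- **Silence is not proof.** The article condenses a fuller protocol, and the sentence on envelopes does not say how they were organised. A stratified draw is not ruled out, and if there was one the percentages do not apply. Still, the sentence is concrete, lets the excluded ward come from the draw, and gives no hint of strata.
- **83% can be over-read.** A reader might infer that arm and specialty are confounded outright in 83% of draws. The figure counts any departure from one ward of each specialty per arm. In (24 + 48)/140 = 51.4% of draws the arms differ by at most one ward, and full separation has probability 5.7%.
- **Random allocation is unbiased on average.** This stands. The issue is the chance imbalance in the one draw that is made.
- **Baseline data exist.** A reader might infer that an imbalance could not be told apart from an effect of guided clinical reasoning. The documents do not support that: 45 records per arm are audited before the intervention, and a stable specialty difference would show there. What remains is that section 3.6 does not carry this information into the comparison of the arms.
- **Matching is not free.** With three pairs the permutation test can no longer reach 0.05, whereas the free draw can just attain it. The plan does not propose such a test, and a model-based analysis need not retain the pairing, so the loss is small but real.
- **It may be too late.** Section 3.7 reports that data were already being collected, so the draw may have been made.

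**Conclusion.** The point holds in a limited form. As described, the draw ignores a known ward characteristic that could be balanced exactly with the same wards. It leaves some specialty imbalance with probability 83%, an intact geriatric or surgical pair in one arm with probability 49%, and no shared specialty with probability 5.7%. The planned separate unpaired tests would let a chance imbalance pass into the post-intervention comparison of the arms.

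This rests on two assumptions: that the 140 draws are equally likely, as the described procedure implies, and that specialty is related to the outcomes, which is plausible but not quantified in the article. The effect on Q-DIO R therefore cannot be sized. The imbalance adds variance; it does not bias the design in a known direction.

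**What to change.** **If the draw is still to come.** Exclude one of the three medical wards by lot, then draw one ward to each arm within geriatric, medical and surgical, and say so in section 3.1. This needs no additional wards, records or staff. The cost is the 1/8 floor on a permutation test that respects the restricted draw, so plan a model-based analysis.

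**If the draw has been made.** State how it was done and report the specialty split by arm. Base the between-group Q-DIO R comparison on post-intervention scores adjusted for each ward's baseline mean, or on change from baseline. The baseline records are already planned, so no new data are required. This removes stable ward differences only as well as 15 baseline records per ward measure them, and not a change over time that differs by specialty. The observations and patient interviews have no baseline (section 4.1), so for them only the split can be reported.

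**Specialty in the model.** Keep this as a sensitivity analysis. At ward level, six wards less two arm means leave 6 − 2 = 4 degrees of freedom. Adjusting for the baseline mean leaves 4 − 1 = 3. Fitting three specialties instead can use two, leaving 4 − 2 = 2, which is too few for the main analysis.

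### Six wards are randomised, but the sample size and the between-arm tests treat records and nurses as independent, so neither the one-sided 5% level nor the stated 70–80% power holds for this design.

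*Protocol article*

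**What the plan says.** - **Allocation (3.1).** Seven wards are eligible, from geriatrics, internal medicine and surgery. By sealed envelope, "three wards will be randomly allocated to the experimental group, three to the control group and one will be excluded".
- **Sample size (3.2.2).** The basis is "tests for unpaired samples (one‐sided"), applied to single records. The diagnoses sub-concept is sized at 32 per arm (standardised effect 0.63, 80% power). The article then states: "For nursing interventions, 45 records (effect size, 0.53; power, 80%) are required". The outcomes sub-concept is sized at 44 per arm, with an effect of 0.47 and only 70% power.
- **Sampling (3.2.2).** At each time point "15 nursing records will be selected per ward", which gives 45 per arm before and 45 per arm after. The only reason given for the per-ward quota is balance between the groups.
- **Analysis (3.6).** If the Q-DIO R scores are normally distributed, unpaired t-tests compare pre- and "postintervention scores and to compare the experimental and control groups". Knowledge and PND scores are compared between arms by Mann–Whitney tests on individual nurses. "All tests will be evaluated one‐sided (levels of significance 0.05").
- **Ward-level data (3.5.1.7).** Organisational characteristics are collected to control for system influences, but 3.6 uses them only in correlations.
- **Limitations (4.1).** Clustering is not mentioned.

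**The concern.** Records and nurses are nested in the wards that were randomised. The article itself gives reasons to expect them to be correlated within a ward. The Background names supervisors' attitude, turnover, workload and nursing organisation as influences on how the nursing process is performed. Section 3.2.1 includes all ward managers so that their behaviour carries over to their teams. Section 3.3 delivers the case meetings to whole ward teams.

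With three wards per arm, a test on single records cannot separate an effect of GCR from a chance difference between two sets of three wards. It takes its standard error from variation between records, whereas the arm difference also carries variation between wards. Hypotheses 1 and 3 are between-arm claims, and the Conclusion ties practice recommendations to whether the hypotheses are supported. A false positive would therefore have consequences. The power quoted for the trial belongs to a different, individually randomised design.

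**Working it through.** **Inputs.** From the article: 3 wards per arm; m = 15 records per ward per time point, so 45 per arm; one-sided α = 0.05; standardised effects d = 0.63, 0.53 and 0.47 with stated power 80%, 80% and 70%; 92 nurses on six wards for the PND (92/6 ≈ 15 per ward); 17 nurses per arm for the knowledge test (17/3 ≈ 6 per ward). Assumed, because the article gives none: ICC from 0 to 0.20.

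**1. The plan's own figures.** The normal approximation n = 2(z₀.₉₅ + z_power)²/d² gives:
- diagnoses: 2(1.645 + 0.842)²/0.63² = 31.2, rounded up to 32
- interventions: 2(1.645 + 0.842)²/0.53² = 44.0, rounded up to 45
- outcomes: 2(1.645 + 0.524)²/0.47² = 42.6, rounded up to 43

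The exact one-sided t-test gives 31.9, 44.7 and 43.3, which round up to the stated 32, 45 and 44. The stated numbers therefore contain no allowance for wards. With the planned 45 per arm, power under independence is 91/80/71%.

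**2. Design effect.** DE = 1 + (15 − 1) × ICC. At ICC 0.05, DE = 1.7 and the effective sample is 45/1.7 = 26.5 records per arm.

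**3. True error of the planned record-level arm comparison.** Approximately 1 − Φ(1.645/√DE). At ICC 0.05 this is 1 − Φ(1.645/√1.7) = 1 − Φ(1.262) = 10.4%. The column below comes from 40,000 simulated trials per ICC and agrees closely.

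**4. Power of a test that keeps the level.** A t-test on six ward means has 2 × 3 − 2 = 4 df, a one-sided critical value of 2.132, and noncentrality d/√(2·DE/45). For interventions at ICC 0.05 this is 0.53/√(2 × 1.7/45) = 1.93, giving power of 48.1%.

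| ICC | DE | True one-sided error, planned t-test | Ward-level power: diagnoses / interventions / outcomes |
|---|---|---|---|
| 0 | 1.00 | 5% | 78.8 / 66.4 / 57.8% |
| 0.02 | 1.28 | 7.3% | 70.0 / 57.5 / 49.5% |
| 0.05 | 1.70 | 10.4% | 59.7 / 48.1 / 41.1% |
| 0.10 | 2.40 | 14.6% | 48.1 / 38.4 / 32.8% |
| 0.20 | 3.80 | 20.6% | 35.6 / 28.5 / 24.6% |
| *Stated* | – | *5%* | *80 / 80 / 70%* |

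**5. Nurse outcomes** (t-test as a proxy for Mann–Whitney). The PND has about 15 nurses per ward, so inflation is similar to that for the records. For the knowledge test, with about 6 per ward, DE = 1 + 5 × ICC. The error is about 1 − Φ(1.645/√1.25) = 7% at ICC 0.05 and 1 − Φ(1.645/√1.5) = 9% at ICC 0.10.

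**6. Could more records repair it?** Not fully. With unlimited records on the same six wards, ward-level power at ICC 0.10 is capped at 64/52/45%. At 15 records per ward, the stated power would need 5/6/6 wards per arm at ICC 0.05 and 6/8/8 at ICC 0.10.

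**The case against.** The mismatch itself is hard to dispute, because the article names both the sample-size basis and the tests. This is not detail left to an unseen analysis plan. The serious objections concern scope and size, and several stand.

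- **Not every test is inflated.** Pre- and post-intervention records come from the same wards, so stable ward effects cancel in the difference. A simulated unpaired pre–post t-test within one arm had one-sided error of 4.6/4.5/4.0% at ICC 0.05/0.10/0.20. It would be inflated only if wards drift differently over time. The problem lies in the between-arm comparisons.
- **The power gap has two causes.** At ICC 0, the drop from 91/80/71% to 79/66/58% comes entirely from having 4 df. Only the further fall comes from within-ward correlation. Both follow from randomising six wards, but they should be reported separately.
- **Diagnoses have some slack,** since 45 records are taken where 32 are needed. Applying the design effect alone, without the 4 df, leaves 84% power at ICC 0.02 and 74% at ICC 0.05. Interventions and outcomes have practically no slack.
- **The planned test would still reject often,** about 85/75/67% of the time at ICC 0.05. It does so with an error rate near 10%. The shortfall applies to a test that keeps the 5% level.
- **The ICC is assumed,** and nothing in the article supports 0.20 in particular. The direction is not in doubt: any positive ICC pushes the error of the arm comparisons above 5%.
- **Baseline records are not used in these power figures.** They describe a post-intervention comparison of ward means. A model that also uses the baseline could do better if ward effects are stable. That gain has not been computed.

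None of these points makes the stated tests valid for ward allocation.

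**Conclusion.** The concern holds, and the plan is wrong as written on this point. The unit of randomisation is the ward, while the sample size and the between-arm tests use the record or the nurse. For the Q-DIO R arm comparison, the nominal 5% one-sided error becomes roughly 7–15% for ICCs of 0.02–0.10. The power of a valid ward-level test on post-intervention means falls to 70/58/50% at ICC 0.02 and 48/38/33% at ICC 0.10. Even with no within-ward correlation, that test falls clearly short of the stated power for interventions (66% against 80%) and outcomes (58% against 70%). For the knowledge test the inflation is smaller, about 7–9% at ICC 0.05–0.10. These sizes depend on the assumed ICC, equal ward sizes and approximately normal scores. This must be corrected before the arm comparisons are interpreted.

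**What to change.** 1. In 3.1, describe the trial as cluster-randomised, with ward as the unit.
2. In 3.6, make ward the unit of inference for all arm comparisons of Q-DIO R, PND and knowledge scores. One option is a t-test on six ward summaries (4 df). The other is a linear mixed model with random ward and ward-by-period effects and small-sample degrees of freedom. Six wards estimate variance components poorly, so the summary-based test is the safer choice for the main result. An exact permutation test over 3 v 3 wards has a smallest one-sided p-value of 1/20 = 0.05, so it can only just reach the stated level.
3. In 3.2.2, restate the calculation with the design effect over a range of ICCs, and give the power that three wards per arm actually deliver.
4. Report the observed ICC for each outcome, and name the small number of wards as a limitation in 4.1.

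The cost is revised analysis wording and a less favourable power statement. No new data or wards are needed. This restores error control but not power: only seven wards are eligible and data collection has started, so the low power has to be disclosed rather than designed away.
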